## Methods/design

### Design

The CHORAL study is a SW-CRT. Each cluster (defined as a single ICU) will be randomly allocated to receive the intervention according to a staggered implementation schedule in one of six sequential steps comprising 2-month intervals. There will be six clusters in total with all clusters commencing with a 2-month control period (baseline) in which standard of care includes chlorhexidine oral care for IVAC prevention. Each cluster will maintain chlorhexidine oral care until they are allocated to crossover from control to intervention according to the randomization schedule. The study completes with a 2-month period during which all clusters have fully de-adopted chlorhexidine and implemented the standardized oral care bundle. Total study duration will be 14 months (Fig. 1). We follow CONSORT cluster trial extension guidelines for SW-RCTs in the design of this study [21]. The SPIRIT checklist is provided in Additional file 2.

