#### Oral health dysfunction

The BOAS scale ranges from 5 to 20, with a score of 5 equivalent to no oral problems and 20 equivalent to the worst possible oral health state. Previous ICU studies report a mean (standard deviation) score of 10 (2) [26]. Taking into account clustering (DEF = 1 + (n − 1) × ICC with an ICC = 0.05 to 0.2), the design effect would range from 3.5 to 10 and therefore the sample size ranges from 86 to 300. We will observe a minimum of 25 patients per ICU at control and intervention phases. With 150 patients in each time period we have 80% power to detect a two-point decrease in the BOAS in the intervention group.

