### Analysis and evaluation

#### Statistical analysis

We will describe our patient cohort and treatment characteristics using means and standard deviations or medians and interquartile ranges dependent on data distribution for continuous variables and frequencies and percentages for categorical variables. To account for clustering of patients within sites, the primary outcome, mortality, will be analyzed using a generalized linear mixed model (with logit link and binary distribution) adjusting for time to account for secular trends as well as important prognostic factors such as age, sex, APACHE III score, and comorbidities. We will inspect missing data and if less than 5% are missing we will use imputation by the median values for the continuous variables and mode for the categorical ones. If more than 5% of the sample has missing values we will use multiple imputations. Differences between the control and intervention periods and time trends will be estimated using OR and their 95% CIs. IVAC counts with offset number of ventilator days per patient will be analyzed using a generalized linear mixed model with log link and Poisson or negative binomial distribution as dictated by the distribution of the data. For mortality and IVAC rates we will exclude those patients who start in the control group and cross-over to the intervention group. BOAS will be summarized using mean and standard deviation and analyzed using linear mixed models (adjusting for clustering of patients within sites) with treatment phase as an independent variable. We will report the CPOT (oral pain during care delivery) scores, and patient self-report (pain, dryness) outcomes, as medians and IQR and analyze using the Wilcoxon rank sum test to compare the pre-intervention and intervention groups.

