#### Pre-and post-intervention oral care fidelity

In the 2 months preceding chlorhexidine de-adoption and implementation of a standardized oral care bundle, and then each month following implementation, trained study team members will collect oral care fidelity data using a structured observational tool on randomized dates. We will observe a minimum of 25 patients per ICU at pre-intervention and intervention phases for a total of 150 patients in each time period. We will report oral care fidelity as medians and IQR and analyze using the Wilcoxon rank sum test to compare the pre-intervention and intervention groups.

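### Pain, dryness and fidelity are compared between phases by an ordinary rank sum test that ignores ICU clustering and calendar time, so its error rate is not controlled

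*Protocol article*

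**What the plan says.** Under Statistical analysis, the protocol article summarises CPOT scores and self-reported pain and dryness "as medians and IQR and analyze using the Wilcoxon rank sum test to compare the pre-intervention and intervention groups". Under Pre-and post-intervention oral care fidelity it repeats the choice: "We will report oral care fidelity as medians and IQR and analyze using the Wilcoxon rank sum test". Neither section names a stratified or clustered version of the test, or any adjustment for ICU or time.

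The data are clustered and ordered in time:

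- Design: "There will be six clusters in total with all clusters commencing with a 2-month control period", followed by staggered crossover in 2-month steps.
- Fidelity section: "We will observe a minimum of 25 patients per ICU at pre-intervention and intervention phases for a total of 150 patients in each time period". The baseline observations fall in the 2 months before each ICU's crossover, "and then each month following implementation, trained study team members will collect oral care fidelity data".
- Pre-intervention phase: self-report is taken only from patients able to give it.

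The other outcomes are treated differently. Mortality gets a mixed model with site clustering and a time adjustment. BOAS, scored at the same bedside observations as CPOT and self-report, gets a linear mixed model that adjusts for site. Its sample size allows for clustering "with an ICC = 0.05 to 0.2", so that "the design effect would range from 3.5 to 10".

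**The concern.** The rank sum test takes its null variance from independent observations. Two features of this design break that assumption.

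1. Patients in one ICU share staff and practice. If an ICU's level moves between its two phases for reasons other than the intervention, all 25 or so patients in a cell move together, and the test reads this as evidence about the intervention. If the ICU's level is fully stable, it cancels from the comparison but stays in the test's variance, and the test is slightly conservative.
2. Every ICU's baseline observations come before its intervention observations. Any general drift in oral care or case mix over 14 months is therefore counted as a phase effect.

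At stake are the inferential statements about pain, dryness and delivery of the bundle. The process evaluation is meant to help interpret the main result, so a chance or secular improvement in fidelity should not be presented as a tested one. This is a choice the protocol makes twice, not a detail left to an analysis plan.

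**Working it through.** The protocol states no error rate or power for these comparisons, so there is no figure to reproduce.

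**Inputs from the protocol article.** K = 6 ICUs; m = 25 patients per ICU and phase (the minimum); ICC 0.05 to 0.2 (stated for BOAS, carried over here as an assumption).

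**Inputs assumed.** Two-sided 5% level; phase-specific share of ICU variance, s, of 0, 0.2 or 0.5; trend of 0 or 0.05 SD per 2-month step; total variance 1.

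**No trend.** The true variance of the phase difference, relative to what the test assumes, is about

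V = m × ICC × s + (1 − ICC), and type I error ≈ 2[1 − Φ(1.96/√V)].

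| s | ICC | V | Approximation | Simulation (4,000 trials) |
|---|---|---|---|---|
| 0 | 0.05 | 0.95 | 4.4% | 4.5% |
| 0 | 0.2 | 0.80 | 2.8% | 3.8% |
| 0.2 | 0.05 | 25×0.05×0.2 + 0.95 = 1.20 | 7.4% | 7.7% |
| 0.2 | 0.2 | 25×0.2×0.2 + 0.80 = 1.80 | 14.4% | 14.2% |
| 0.5 | 0.05 | 25×0.05×0.5 + 0.95 = 1.575 | 11.8% | 11.5% |
| 0.5 | 0.2 | 25×0.2×0.5 + 0.80 = 3.30 | 28.1% | 28.2% |

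**Fewer self-reporters.** With an assumed m = 10, V is 1.05 to 1.20 at s = 0.2 (5.6% to 7.4%) and 1.20 to 1.80 at s = 0.5 (7.4% to 14.4%).

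**With a trend.** Suppose intervention observations are spread evenly over the periods after crossover. The mean gap between an ICU's intervention and baseline observations is then 3.5, 3, 2.5, 2, 1.5 and 1 steps from the first to the last ICU to cross over, on average 13.5/6 = 2.25 steps. At 0.05 SD per step the bias is 2.25 × 0.05 = 0.1125 SD. The standard error that the test assumes is √(2/150) = 0.1155, so the bias is 0.97 standard errors. At ICC 0.1 and s = 0.2, V = 25×0.1×0.2 + 0.9 = 1.4, and the rejection rate is about P(Z > (1.96 − 0.97)/1.183) + P(Z < −(1.96 + 0.97)/1.183) ≈ 20% + 1% = 21%. Simulation gives 18-19%, depending on whether the ICU deviation is drawn per period or per phase. Across ICC 0.05 to 0.2 and s of 0 to 0.5, with the deviation drawn per period, the simulated range at this trend is 13-31%. If observations stay within the 2 months either side of crossover, the gap is one step and the rate at ICC 0.1 is 5.9% (s = 0) to 12.1% (s = 0.2).

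**Candidate remedies, simulated.**

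- ICU-stratified (van Elteren) rank test at ICC 0.2, s = 0.2, no trend: 17-18%, against 14-15% for the plain test. It removes stable ICU differences only.
- Within-ICU paired comparison of means: 4.8-5.2% without a trend, but 5.4-6.7% at 0.05 SD per step and 6.6-12.6% at 0.1.
- Weighted regression of ICU-period means on ICU, linear time and phase: 4.7-5.5% in every setting tried. The simulated trend was itself linear and the weights were correct, so this is a favourable test.

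**The case against.** The case for leaving the plan alone has five parts.

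- **Rank of the outcomes.** Outcome measures lists mortality as primary and IVAC and BOAS as secondary. Pain, dryness and fidelity are neither. This stands, and it limits the weight of the point.
- **Use of fidelity.** A reader might infer that the fidelity p-value decides how a null mortality result is read. The documents do not support that. Fidelity is audited against a 70% compliance threshold and reported as medians and IQR; the level of delivery carries the interpretation.
- **Source of the inflation.** The ICC is given for BOAS only, and the phase-specific share and the trend are not given at all. With stable ICU effects and no trend the test errs by only a point or two, on the safe side. A reader might infer that the p-values are certainly wrong by a large factor; what is shown is that they may be, under plausible inputs that the plan does not exclude.
- **Sample size for self-report.** It is tempting to speak of 300 observations for every outcome. The minimum of 25 per cell applies to observed patients, and only some can self-report, so the figures for m = 25 fit CPOT and fidelity better than dryness and self-reported pain.
- **Unequal counts.** Monthly observation after crossover, a stated minimum only, and more frequent audits where fidelity is low make an unequal ICU mix between phases possible. No counts are given, so no figure here rests on it.

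None of this defends the test itself. The same paragraph adjusts BOAS for site and mortality for site and time, and gives no reason to treat outcomes from the same observations as independent.

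**Conclusion.** The point holds as an inconsistency in a stated analysis. For CPOT pain, self-reported pain and dryness, and fidelity, the ordinary rank sum test does not control its error rate in this design. At nominal 5%, with 25 per cell and ICC 0.05 to 0.2, type I error runs from about 3-4% (fully stable ICU effects) through 7-14% (20% phase-specific) to 11-28% (half phase-specific). It falls with smaller self-report cells and rises with a secular trend. The ICC is borrowed from BOAS; the phase-specific share and the trend are assumptions. The possible inflation matters more than the slight conservatism. The analysis should be changed, but the point is not critical to the trial: it gives no ground for doubting the mortality, IVAC or BOAS conclusions.

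**What to change.** Replace the rank sum test in both sections by a mixed model: linear or ordinal for scores and fidelity, logistic for CPOT above 2. Include random effects for ICU and ICU-by-phase, fixed effects for treatment phase and calendar time, and a small-sample correction for six clusters. An equivalent regression of ICU-period means with ICU, time and phase terms is an acceptable and simpler alternative. Keep medians and IQR as description.

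Two cautions. Copying the BOAS model is not sufficient, because as described it has site and phase but no time term and no ICU-by-phase effect. The van Elteren test should not be offered as a minimum, because it corrects neither phase-specific ICU variation nor time.

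The cost is a wording change, a little more analysis work, and wider, honest intervals. With 12 ICU-by-phase cells the ICU-by-phase variance will be imprecisely estimated, which is why the small-sample correction is needed. No new data are required.

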### Process evaluation

Our embedded mixed methods process evaluation will examine the reach of oral care intervention education, stakeholder response to chlorhexidine de-adoption and implementation of a standardized oral care bundle, and fidelity of oral care processes [22].

#### Pre-and post-intervention oral care fidelity

In the 2 months preceding chlorhexidine de-adoption and implementation of a standardized oral care bundle, and then each month following implementation, trained study team members will collect oral care fidelity data using a structured observational tool on randomized dates. We will observe a minimum of 25 patients per ICU at pre-intervention and intervention phases for a total of 150 patients in each time period. We will report oral care fidelity as medians and IQR and analyze using the Wilcoxon rank sum test to compare the pre-intervention and intervention groups.

#### Pre-and post-intervention qualitative interviews

During pre-intervention and end-of-study periods, we will recruit and interview eligible (i.e., working in a participating unit for ≥ 3 months) ICU nurses, respiratory therapists, pharmacists, physiotherapists, speech-language pathologists, and physicians. Pre-intervention interviews will target current oral care practices in addition to anticipated barriers and facilitators to the de-adoption of chlorhexidine and implementation of a standardized oral care bundle. End-of-study interviews will address the reach of the educational delivery, stakeholder response to the intervention, perceptions of oral care bundle fidelity, and contextual factors (e.g., secular trends) impacting the study. Sixty clinician interviews (ten per site) in each time period will occur by telephone or in person at the hospital, based on participant preference. We will use qualitative content analysis (CA), a method for describing the content of communication in an objective and systematic manner for transcribed clinician interviews [33]. Two investigators will independently code interviews to enhance rigor.

## Discussion

To our knowledge, the CHORAL study is the first SW-CRT designed to evaluate the effect of de-adopting chlorhexidine oral rinse and implementation of a standardized oral care bundle on ICU mortality, IVACs, and oral health status. In response to multiple independent meta-analyses suggesting the possibility of harm, we aim to conduct a large prospective trial with sufficient statistical power to detect mortality differences between patients receiving chlorhexidine oral care and those receiving non-chlorhexidine oral care. The prospective nature of the trial is important as the mortality signal of concern is only present in meta-analyses [10, 11].

Clear evidence regarding the effect of oral chlorhexidine de-adoption on our primary outcome of mortality will clarify concerns of preventable harm. Secondary outcomes, including IVAC rates and oral health status following the de-adoption of oral chlorhexidine and delivery of a standardized oral care bundle, will enhance knowledge regarding the impact of our intervention on patient-centered outcomes, including infection and oral health dysfunction. As chlorhexidine is presently identified as an indicator of high-quality ICU care [6], our study results will prompt re-examination of professional society guidelines.

We have chosen a SW-CRT design due to the expressed desire of participating clusters to de-adopt chlorhexidine and the requirement to deliver the intervention and measure outcomes at the level of individual patients and at the level of the cluster. The CHORAL study introduces a substantial change in longstanding oral care practices which requires provision of education to large groups of care providers across discrete units. An important advantage of the study design is the ability to deliver education in smaller groups (clusters) at pre-defined time-points. This approach will avoid contamination between intervention and control groups seen in parallel randomized controlled trial (RCT) design and alleviate ethical concerns about withholding or blinding of interventions in RCTs.

As effective methods to de-adopt established ICU practices are unclear, our process evaluation will provide clinicians and policy makers with vital information about how the intervention was actively delivered [18]. This is important as ambiguity regarding the composition and delivery of ICU processes threatens interpretation, replication, and research investment. In addition, our embedded process evaluation will clarify helpful strategies for effective education, thereby supporting future integration of oral care interventions across varying practice contexts [29].

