Maintenance oral care Q4 hours and PRN	Equipment	Procedure
Mouth and lip moisturizer	•As above	•As above
Oral secretion removal	•As above	•As above

*CPOT* Critical-Care Pain Observational Tool, *HOB* head of bed, *PRN* pro re nata or “as needed”

The following oral care interventions will commence in the intervention phase for each step and become standard of care:
Intervention 1 (oral chlorhexidine de-adoption): Each cluster will de-adopt oral chlorhexidine from routine practice for all invasively ventilated patients. Use of routine oral chlorhexidine will not be permitted during the intervention period with the exception of patients prescribed chlorhexidine for non-standard care.Intervention 2 (oral care protocol): This two-part, nurse-led intervention incorporates comprehensive and maintenance oral care activities. Comprehensive care involves twice daily (morning and evening) a) oral assessment (inspection of the oral space, teeth and gums); b) tooth brushing; c) oral/lip moisturization; and d) suctioning oropharyngeal secretions above the cuff. Maintenance care involves, at a minimum of every 4 h and as needed, a) oral/lip moisturization; and b) suctioning oropharyngeal secretions above the cuff (Table 1).

One month after allocation to the intervention, a trained assessor will begin to observe fidelity of delivery of the oral care protocol and assess patient oral health status using the BOAS, CPOT, and patient self-report of oral health symptom intensity on randomly selected dates. We will provide each cluster lead with written feedback on these observations for dissemination to frontline ICU staff. For sites identified as having low intervention fidelity during audits (< 70% compliance across all bundle components), we will provide additional education and intensified audit frequency. We estimate observing a minimum of 25 patients in each ICU during the intervention phase (150 total).

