### Sample size

#### Mortality

Recent systematic reviews [30] show that chlorhexidine increased mortality with an odds ratio (OR) of 1.25 (95% confidence interval (CI) 1.05–1.50). This corresponds to a risk ratio of 1.18 (95% CI 1.04–1.33) and an absolute reduction in mortality of 5% (95% CI 1%–6%). Six clusters averaging 50 ventilated patients per month for 14 months for a total of 4200 patients, assuming an intracluster correlation (ICC) of 0.001, provides about 80% power to detect an absolute reduction in mortality of 5.5% from a baseline rate of 26% [6, 31, 32].

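### The trial estimates the joint mortality effect of stopping chlorhexidine and starting the oral care bundle, so the Discussion's promise of clear evidence on de-adoption alone is not supported.

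*Protocol article*

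**What the plan says.** The section on the intervention phase introduces two components and gives them one start: "The following oral care interventions will commence in the intervention phase for each step and become standard of care".

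- Component 1: "Each cluster will de-adopt oral chlorhexidine from routine practice for all invasively ventilated patients". Chlorhexidine prescribed outside routine care is the only exception.
- Component 2: "This two-part, nurse-led intervention incorporates comprehensive and maintenance oral care activities". These are assessment, brushing, moisturizing and suction twice a day, plus moisturizing and suction at least every four hours.

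Under Design, each ICU keeps chlorhexidine until its own crossover, and "The study completes with a 2-month period during which all clusters have fully de-adopted chlorhexidine and implemented the standardized oral care bundle". Both research questions ask about the two components together. Under Statistical analysis, mortality is analysed with a logistic mixed model adjusted for time, and the control and intervention periods are compared by an odds ratio.

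The Discussion opens by naming both components, and later says of the primary outcome: "Clear evidence regarding the effect of oral chlorhexidine de-adoption on our primary outcome of mortality will clarify concerns of preventable harm". The next sentence, on the secondary outcomes, names both components again.

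**The concern.** For mortality, the Discussion states a conclusion about one component of a two-component intervention, and the schedule never varies the components separately. The sentence also ties that conclusion to preventable harm, and the same paragraph expects the results to lead to a fresh look at professional guidelines.

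A fall in mortality could then be reported as proof that chlorhexidine was harmful, although some of it may come from better oral care. A null result could be reported as reassurance about chlorhexidine, although a gain from one component may have cancelled a loss from the other. In both cases the analysis would be sound and the inference drawn from it would not be.

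**Working it through.** **1. The plan's own figure.** The sample size section gives about 80% power for a fall from 26% to 20.5% (5.5 points), with 6 ICUs, 50 patients per month, 14 months (4200 patients) and an ICC of 0.001. The Hussey-Hughes variance for a stepped wedge is

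Var = Iσ²(σ² + Tτ²) / [(IU − W)σ² + (U² + ITU − TW − IV)τ²].

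- I = 6 ICUs, T = 7 periods, 100 patients per ICU-period. U = 21 intervention ICU-periods; W = V = 91 (sums of squared column and row totals of the schedule).
- Pooled risk 0.2325, so the binary variance is 0.2325 × 0.7675 = 0.1784. Then σ² = 0.1784/100 = 0.001784 and τ² = (0.001/0.999) × 0.1784 = 0.000179.
- IU − W = 126 − 91 = 35. U² + ITU − TW − IV = 441 + 882 − 637 − 546 = 140.
- The standard error is 0.01927. With two-sided alpha 0.05 (assumed; the article gives none), 0.055/0.01927 − 1.96 = 0.89, a power of 81.4%.

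Using the baseline variance instead gives 78.5%. The stated power reproduces and is not in dispute. The question is which effect it refers to.

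**2. What the schedule contains.** 6 ICUs × 7 periods = 42 ICU-periods. Intervention periods per ICU are 6, 5, 4, 3, 2 and 1, a total of 21. The other 21 are control. None is planned with chlorhexidine stopped and the bundle not started, or with the bundle started and chlorhexidine continued. The education kit reaches staff two weeks before crossover, but the plan dates both components from the intervention phase.

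**3. What can be estimated.** Let R = 1 when chlorhexidine is withdrawn and B = 1 when the bundle is in place. By plan, R = B in all 42 ICU-periods.

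- 6 ICU terms + 6 period terms + R + B: 14 columns, rank 13.
- 6 ICU terms + 6 period terms + one combined term: 13 columns, rank 13.

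Only the joint effect is estimable. A larger sample does not change this, and neither does adjustment for age, sex, APACHE III score or comorbidity.

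**4. What a result would leave open.** On an additive scale, joint effect = withdrawal effect + bundle effect. The bundle effects below are assumptions for illustration; the article gives none.

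| Joint change (points) | Assumed bundle effect | Implied withdrawal effect |
|---|---|---|
| −5.5 | 0 | −5.5 |
| −5.5 | −2 | −3.5 |
| −5.5 | −5.5 | 0 |
| −5.5 | +2 | −7.5 |
| 0 | −2 | +2 |

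The mortality data fit every row with the same joint change equally well. That does not make those rows equally plausible.

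**The case against.** The best defence is that the operative text is already right. The title, abstract, research questions, Design section and opening of the Discussion all name the combined strategy, and the model estimates exactly that. No estimand, sample size or decision rule depends on the challenged sentence, which could be read as shorthand for the whole intervention. This limits the point to the stated conclusion. It does not remove it: that sentence concerns the primary outcome, drops the bundle where its neighbour keeps it, and claims to settle a question of harm.

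Several stronger readings are tempting, and the article does not support them.

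- A reader might infer that the conclusion is wrong whatever the result. It is unsupported, not necessarily false: if the bundle has no effect on mortality, attribution to chlorhexidine is correct.
- A reader might infer that the control periods have no bundle care. The section on oral care observations plans to document baseline oral care delivery, so some elements may already be in use, and the contrast in component 2 may be smaller than it looks.
- A reader might take a fall due wholly to the bundle as being as likely as one due wholly to chlorhexidine. The Background puts mortality attributable to VAP at only 1%, which makes a 5.5-point effect through VAP prevention alone hard to support. The Background also links oral care to systemic outcomes and to longer ventilation, so a smaller bundle effect cannot be dismissed.
- A reader might see the same error where the Discussion aims to "detect mortality differences between patients receiving chlorhexidine oral care and those receiving non-chlorhexidine oral care", or where the sample size rests on a review in which "chlorhexidine increased mortality with an odds ratio (OR) of 1.25". The first fairly describes the package contrast, since the bundle is oral care without chlorhexidine. The second takes a planning value from available evidence. Neither attributes the trial's result to one component.
- A reader might think all ICUs switch at once. The switch is simultaneous only within an ICU; crossovers are two months apart.

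It is also true that oral care fidelity will be observed before and after crossover in at least 25 patients per ICU per phase, and that the process evaluation is meant to help interpret the results. It is not described as separating the two effects.

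**Conclusion.** The point stands as a correction to what the trial may conclude on its primary outcome. The design answers the research questions as posed, namely the joint effect of withdrawal and bundle. It does not provide clear evidence on de-adoption alone, and it cannot by itself show or exclude harm from chlorhexidine.

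The size is a matter of identification: 0 of 42 planned ICU-periods separate the components, and the model with both terms is one rank short. How large the resulting error of attribution could be is unknown, because it depends on how much non-chlorhexidine care changes at crossover and on whether that change affects mortality. The article gives neither figure.

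This rests on the ICUs following the planned schedule. Chlorhexidine prescribed outside routine care during intervention periods does not alter it, because that use is not randomized.

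**What to change.** In the Discussion, reword the mortality conclusion so that the result is the effect of the combined strategy: chlorhexidine withdrawal plus the standardized bundle, compared with usual care including chlorhexidine. Add one sentence stating that the component effects cannot be separated, so the result cannot on its own show or exclude harm from chlorhexidine, and a null result could reflect opposing effects. Any statement about guidelines should then refer to the strategy as a whole.

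Optionally, report the planned before-and-after fidelity observations by bundle component (assessment, brushing, moisturizing, suction) beside the mortality result. With about 25 patients per ICU per phase this is descriptive context on how much other care changed, not a way to divide the effect.

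The cost is a narrower claim and, if the option is taken, one table from data already planned. Design, sample size and primary analysis are unchanged.
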